## Abstract

**Background:**

Alpha-mannosidosis is a lysosomal storage disorder caused by reduced enzymatic activity of alpha-mannosidase. SPARKLE is an alpha-mannosidosis registry intended to obtain long-term safety and effectiveness data on the use of velmanase alfa during routine clinical care in patients with alpha-mannosidosis. It is a post-approval commitment to European marketing authorization for Velmanase alfa (Lamzede^®^), the first enzyme replacement therapy for the treatment of non-neurologic manifestations in patients with mild to moderate alpha-mannosidosis. In addition, SPARKLE will expand the current understanding of alpha-mannosidosis by collecting data on the clinical manifestations, progression, and natural history of the disease in treated and untreated patients, respectively.

**Results:**

The SPARKLE registry is designed as a multicenter, multinational, noninterventional, prospective cohort study of patients with alpha-mannosidosis, starting patient enrollment in 2020. Patients will be followed for up to 15 years. Safety and effectiveness as post-authorization outcomes under routine clinical care in patients with treatment will be evaluated. The primary safety outcomes are the rate of adverse events (anti-velmanase alfa-immunoglobulin G antibody development, infusion-related reactions, and hypersensitivity). Secondary safety outcomes include the evaluation of medical events, change in vital signs, laboratory tests, physical examination, and electrocardiogram results. The primary effectiveness outcome is a global treatment response rate, evaluated as the individual aggregate of single endpoints from pharmacodynamic, functional, and quality-of-life effectiveness outcomes; secondary effectiveness outcomes are to characterize the population of patients with alpha-mannosidosis with regard to clinical manifestation, progression, and natural history of the disease. Any patient in the European Union with a diagnosis of alpha-mannosidosis who is willing to participate will likely be eligible for inclusion in the registry. Publications to disseminate scientific insights from the registry are planned.

**Conclusion:**

This study will provide real-world data on the long-term safety and effectiveness of velmanase alfa in patients with alpha-mannosidosis during routine clinical care and increase the understanding of the natural course, clinical manifestations, and progression of this ultra-rare disease.

## Background

Alpha-mannosidosis (OMIM 248500) is an ultra-rare monogenic disorder caused by alpha-mannosidase deficiency (Enzyme Commission number: 3.2.1.24) and has an estimated worldwide prevalence of 1:500,000–1:1,000,000 live births [1]. However, as alpha-mannosidosis is an underdiagnosed disease, the real prevalence may be higher [2]. Alpha-mannosidosis is an autosomal recessive, lysosomal-storage disease resulting from mutations in the *MAN2B1* gene, located on chromosome 19 (19 p13.2-q12) [3]. As alpha-mannosidase is a lysosomal enzyme involved in glycoprotein catabolism, reduced activity results in impaired degradation of glycoproteins and leads to an accumulation of mannose-rich oligosaccharides in various tissues [4].

Intracellular accumulation of mannose-rich oligosaccharides leads to different clinical symptoms, including hearing impairment, intellectual disabilities, impairment of motor function and speech development, recurrent infections, immunodeficiency, skeletal abnormalities, destructive polyarthropathy, muscular weakness, ataxia, and psychiatric disease [1]. Alpha-mannosidosis presents in a continuum of clinical symptoms and is a heterogeneous disorder due to the varied manifestations and their different severity, as well as various rates of progression in individual patients [5]. In the majority of patients, the disease is clinically recognized in the first decade of life, progression is slow, and ataxia develops between the ages of 20–30 years [1].

Long-term enzyme replacement therapy (ERT) is a therapeutic option for alpha-mannosidosis [6] and velmanase alfa is the first human recombinant form of alpha-mannosidase available for ERT. To date, velmanase alfa (Lamzede^®^, ChiesiFarmaceutici S.p.A., Parma, Italy) is the only authorized treatment for alpha-mannosidosis in Europe; it is approved for the treatment of non-neurologic manifestations in patients with mild to moderate alpha-mannosidosis [7]. Velmanase alfa targets the underlying cause of the disease by breaking down mannose-rich oligosaccharides that would otherwise accumulate in the lysosome [8]. The velmanase alfa molecule has an identical structure to naturally occurring alpha-mannosidase and is approved for use at 1 mg/kg body weight once weekly as an intravenous infusion [7]. After infusion, velmanase alfa is taken up by cells and transported to the lysosomes, where it replaces the patient’s defective enzyme and thus reduces levels of accumulated oligosaccharides [8]. Velmanase alfa also has Orphan Drug designation in the United States and Europe.

In clinical trials, patients with alpha-mannosidosis treated with velmanase alfa achieved improvements in biomarkers, motor function, pulmonary function, immunologic profile, and quality of life (QoL) [4, 6, 9]. Importantly, a novel global treatment-response model composed of pharmacodynamic, functional, and QoL outcomes was applied post hoc to data from the pivotal randomized controlled trial (RCT) of velmanase alfa in patients with alpha-mannosidosis (NCT01681953) and the longer-term integrated data from all patients in the clinical development program. A global response required positive responses in at least two outcome domains of the model [4]. In the pivotal RCT, 13 of 15 patients (86.7%) treated with velmanase alfa achieved a global response compared with 3 of 10 patients (30.0%) who received placebo [4]. Similarly, in the integrated data set, 29 of 33 treated patients (87.9%) were global responders (100% of pediatric patients [*n* = 19] and 71% of adults [*n* = 10]) [4].

Patient registries are organized systems for collecting information that can provide uniform data for a population defined by particular diseases [10]. Establishing registries, such as those in the European Reference Networks for patients who have complex conditions [11] and the Unified European Registry for Inherited Metabolic Disorders [12], contributes to increased opportunities for coordinating regional healthcare expertise to improve the knowledge of natural disease history, and also to evaluate efficacy and safety over the long term in patients with a new treatment. SPARKLE is an alpha-mannosidosis disease registry study intended to obtain long-term safety and effectiveness data on the use of velmanase alfa during routine clinical care in patients with alpha-mannosidosis and is a post-approval commitment to marketing authorization in Europe.

## Methods

### Study design

SPARKLE is a post-authorization safety and efficacy registry in Europe, designed as a multicenter, international, prospective cohort study of patients with alpha-mannosidosis (Fig. 1). The primary objective is to assess the long-term effectiveness and safety of treatment with velmanase alfa under conditions of routine clinical care; secondary objectives include expanding the current understanding of alpha-mannosidosis by collecting data to characterize the natural history of the disease. Source data will be collected by the investigator in the patient file and captured in an electronic case report form (eCRF). This also includes data from patients receiving treatment in a home-care setting. The study, which started patient enrollment in 2020, has an indefinite recruitment period. Patients will be followed for up to 15 years after inclusion. The end of the study is defined as the last visit of the last patient registered in the study. The study will be conducted under conditions of routine clinical practice, according to the treating physician, without mandatory registry assessments. Patients are eligible for the study irrespective of treatment (velmanase alfa, hematopoietic stem cell transplantation or any biologic substance received as part of a clinical trial during participation in the registry).

**Fig. 1 Fig1:**
[figure not shown]
Study design. *VA* velmanase alfa. ^a^If applicable in accordance with routine clinical practice, unscheduled follow-up visits can be performed at, but not limited to, 3 months after VA treatment start, or whenever deemed appropriate according to clinician judgment for patients who start VA treatment within 1 year prior to registry inclusion. ^b^If a patient is transferred to another continuing care site during the 15-year observational period, the new treating site will be formally involved in the registry following a request of authorization submitted to the relevant ethics committee and regulatory authority to complete the 15-year observational period. ^c^Patients can start VA treatment at any time during the course of their participation in the registry; if applicable in accordance with routine clinical practice, the baseline visit should be repeated before administration of VA and unscheduled visits recommended as reported in the schema above

The study will be conducted in accordance with the Declaration of Helsinki, International Council for Harmonisation Good Clinical Practice, Good Pharmacovigilance Practice, and all other applicable laws and regulations of each country in which the research is carried out. The study will also be conducted in accordance with the Strengthening the Reporting of Observational Studies in Epidemiology (STROBE) guidelines. Results of the study will be reported in accordance with the Methodological Standards in Pharmacoepidemiology of the European Network of Centres for Pharmacoepidemiology and Pharmacovigilance (ENCePP) [13]. This is an observational non-interventional study capturing only data from routine clinical practice. Participation in the study will not change the patient–physician relationship, nor influence the physician’s drug prescription or therapeutic or other management of the patient.

### Patient population

Any patient in the European Union with a genetic confirmed diagnosis of alpha-mannosidosis who is willing to participate will be eligible for inclusion. Inclusion criteria are limited to a signed and dated informed consent form, including agreement to permit the Investigator to enter assessment data in the registry that has been recorded prior to inclusion in the registry, which has been obtained from the patient’s medical record. The inclusion form is signed by the patient, parents or a legally acceptable representative according to local regulation. There are no exclusion criteria for patients with this disease. Alpha-mannosidosis and its treatment will progress over the duration of the study and the study protocol may be amended as necessary. Patients’ informed consent will be required for any substantial changes.

Populations for analysis include a velmanase alfa and a no-velmanase alfa safety and efficacy analysis set. The velmanase alfa safety analysis set includes all patients in the registry who have, at some time, received any study drug treatment with a minimum individual follow-up of ≥ 1 month after the last dose. The velmanase alfa efficacy analysis set consists of patients in the same safety analysis set with efficacy evaluations during velmanase alfa treatment and for 12 months thereafter. The no-velmanase alfa safety analysis set includes patients only for the time when they are not, and have not within 1 month, been taking velmanase alfa. The no-velmanase alfa efficacy analysis set includes patients only for the time when they are not, and have not within 12 months, been taking velmanase alfa.

### Baseline and demographic variables

At the registry baseline visit (first visit after inclusion), it is suggested that the following information will be reported in the eCRF: demographics (ethnicity, age, sex), medical and disease history, genotype mutations, concomitant illnesses, previous and concomitant medications and medical procedures, physical examination (including the ability to perform the endurance test and a hearing test), vital signs, and anthropometric measurements. For patients treated with velmanase alfa, the baseline data would be taken from the time treatment was initiated in order to provide a baseline for safety and effectiveness evaluations. Therefore, it is recommended to repeat a treatment baseline visit, if in accordance with routine clinical practice, in patients starting velmanase alfa treatment at any point during participation in the registry.

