^d^Patients’ retrospective data may be collected at the time of registry enrolment if available. Baseline visits are recommended to be repeated for those patients who will start VA therapy during the course of the study, before therapy is initiated

^e^Physical examination to collect vital signs, anthropometric measurements like height, weight, rate of growth, and the ability to perform the endurance test at the study visit

^f^If applicable, information regarding weekly VA therapy received by the patient need to be recorded within all the registry duration

^g^All assessments mentioned in the above table will be collected only if considered necessary and available as part of routine clinical practice by the treating physician; no additional tests specific to the registry will be done

^h^Standard test for hematology assessed by local laboratory if available per clinical practice of the site: hemoglobin, hematocrit, platelet count, red blood cells, and white blood cells with differential count (all expressed in %, as well as in absolute numbers)

^i^Standard test for hematology assessed by local laboratory if available per clinical practice: serum electrolytes, creatinine, creatine-kinase, amylase, AST, ALT, ALP, albumin, bilirubin (total and direct), LDH

^j^The markers (oligosaccharides in serum, IgG, IgA, and ADA) will be evaluated through a central laboratory in European countries other than Germany. In Germany, marker testing will take place according to local routine clinical practice

^k^In patients 4 years and older, and when applicable according to the judgment of treating physician

^l^In patients under 4 years of age and when applicable according to the judgment of treating physician

^m^AEs/ADRs based on all risk categories associated with VA European RMP, including infusion-related reactions and hypersensitivity (as identified risks), acute renal failure, loss of consciousness and medication errors (as potential risks). Data on pregnancy (including birth and newborn data) and lactation (as missing information) will be also collected if available

^n^One of the behavior checklists (CBCL pre-scholar/scholar, ABCL/ASR [self-reporting], OABCL) will be used to the applicable age and according to the judgment of treating physician

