### Statistical analyses

Baseline demographic and disease characteristics will be presented by means of descriptive statistics and frequency distributions, as appropriate. Descriptive safety outcomes will be presented and summarized over time. For AEs, both the frequency of patients with an AE and the number of events will be presented by year from baseline. Safety variables will be presented based on person-years at risk. Effectiveness variables will be summarized by means of descriptive statistics or frequency of distribution, as appropriate, and all variables (actual values and change from baseline, if applicable) will be presented by time point. The effects of baseline characteristics on effectiveness will be evaluated by means of regression/logistic models. Covariates in the model will be age (< 18 and ≥ 18 years), sex (male, female), sibships, genotype (Groups 1, 2, and 3, per Borgwardt et al.) [18], residual enzymatic activity (< 10, 10 to < 15, and ≥ 15 nmol/h/mg), and Childhood Health Assessment Questionnaire Disability Index (0–1, 1–2, and 2–3).

Provided that a sufficient number of nontreated patients with adequate data are enrolled, a comparison will be conducted between the velmanase alfa-treated and nontreated groups. Propensity score (PS) analysis will be used to compare GTRs after 3 years; the PS will be calculated as the predicted probability of response using logistic regression, with the same covariates as used for the baseline characteristics regression. Subgroup analyses may be performed depending on overall sample size; results will be presented descriptively.

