SPARKLE is part of a growing number of rare disease registries, with over 750 listed in Europe as of May 2019 [20]. SPARKLE will contribute to the increasing database of information gathered from lysosomal storage disease registries, including those for Fabry disease, Pompe disease, Gaucher disease, and mucopolysaccharidoses [21, 22], as well as the almost 40 registries/databases that may include patients with alpha-mannosidosis registered with Orphanet [21]. Importantly, SPARKLE is the only ongoing registry study specifically designed for alpha-mannosidosis; it will provide a much-needed data set relating to this disease, and benefits from several strengths. The protocol adheres to the rare disease registry guidelines suggested by the International Rare Diseases Research Consortium [23] and recommendations of the European Union Committee of Experts on Rare Diseases [24]. Existing treatment registries that evaluate orphan medicinal products for the treatment of lysosomal storage disorders are often limited by incompleteness and variable quality of the data [25]. The eligibility criteria for participation in SPARKLE are minimal in order to allow the largest possible number of patients to participate, and methodologic rigor will be exercised to ensure the highest-quality data and data analysis. In addition, SPARKLE is the only European alpha-mannosidosis-specific registry; it is designed to collect both safety and efficacy data in treated patients, as well as information on patient and disease characteristics. It is not restricted to patients receiving a particular treatment, or a time when treatment is initiated.

Some limitations need to be acknowledged. As information in the registry will be collected during routine clinical care, the assessments performed and data collected may vary from center to center, as may the interpretation of data by the individual Investigators. In addition, potential bias of unknown size and direction could be introduced by patient self-selection into the study and by the fact that some patients with alpha-mannosidosis may be treated in centers not participating in the registry.

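### Back-dated early results from patients already on velmanase alfa at inclusion may bias the by-time-point effectiveness summaries; show them separately and use delayed entry

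*Protocol article*

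**What the plan says.** Five statements in the protocol article bear on this point.

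- **Time origin** (Baseline and demographic variables): for patients on velmanase alfa, "the baseline data would be taken from the time treatment was initiated in order to provide a baseline for safety and effectiveness evaluations".
- **Entry** (Discussion), describing the registry: "It is not restricted to patients receiving a particular treatment, or a time when treatment is initiated".
- **Pre-inclusion data** (Patient population): consent covers permission for the investigator to "enter assessment data in the registry that has been recorded prior to inclusion in the registry". Data management likewise allows retrospective data from the medical record.
- **Analysis set** (Patient population): the velmanase alfa safety set "includes all patients in the registry who have, at some time, received any study drug treatment", subject to a minimum follow-up, and the efficacy set "consists of patients in the same safety analysis set with efficacy evaluations during velmanase alfa treatment" and for 12 months afterwards. Neither requires treatment to begin after inclusion, and neither sets a rule for when a previously treated patient starts to count.
- **Analysis** (Statistical analyses): effectiveness is summarised descriptively, and "all variables (actual values and change from baseline, if applicable) will be presented by time point". No distinction is made between patients who started before inclusion and those who started after it.

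The primary effectiveness outcome is narrower. Under Effectiveness variables and Study size, the GTR is assessed after 3 years of treatment in patients who are velmanase alfa-naïve. The article does not say whether naïve refers to registry inclusion or to the start of treatment.

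**The concern.** Taken together, these rules produce left truncation. A patient who enrols two years after starting treatment can fill the year-1 and year-2 cells of the effectiveness tables from old records. A comparable patient who died before enrolment fills no cell, and one who left care is unlikely to fill any. Patients who start during the registry are followed forward from their first dose and carry no such condition.

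Pooling the two groups has two consequences. If leaving care before inclusion is related to response, the previously treated part of an early time point does not represent starters in general. The share of previously treated patients will also differ between time points, so an apparent time course can partly reflect a change in who is being summarised.

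This matters because the registry is a post-approval commitment on long-term effectiveness, and these tables are where the course of response over time will be read.

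**Working it through.** **The plan's own figure.** The article gives no figure for the time-point summaries. Its only effectiveness calculation is Table 4. Clopper–Pearson limits for 42 responders out of 70 (0.60 × 70) are 0.476 to 0.715, width 0.239, as printed, and the other four rows also reproduce. Table 4 concerns the GTR and is not altered by this point.

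**Step 1: does selection alone create bias?** Let p be the true response, and let rR and rN be the probabilities that a responder and a non-responder can still be enrolled when inclusion comes. Observed response among back-dated patients is

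p·rR / [p·rR + (1 − p)·rN].

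The article gives neither rR nor rN, so all values below are assumptions. With p = 0.60:

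| rR | rN | Back-dated patients | Half back-dated, half new starters |
|---|---|---|---|
| 0.95 | 0.95 | 0.600 | 0.600 |
| 0.95 | 0.90 | 0.613 | 0.606 |
| 0.95 | 0.80 | 0.640 | 0.620 |
| 0.95 | 0.60 | 0.704 | 0.652 |
| 0.85 | 0.95 | 0.573 | not computed |

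For example, 0.60 × 0.95 = 0.570 and 0.40 × 0.60 = 0.240, so 0.570/0.810 = 0.704. The last row is 0.510/(0.510 + 0.380) = 0.573. Bias is zero when exit is unrelated to response, and it reverses when responders are the less likely to enrol.

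**Step 2: what does back-dating add to ordinary attrition?** Assume a constant annual exit rate h (2% in responders; 2, 5, 10 or 20% in non-responders) and inclusion uniformly 0 to D years after treatment start. A back-dated patient supplies a year-1 value if still present at both year 1 and inclusion. For D > 1 this has probability

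S(h) = [e^(−h) + (e^(−h) − e^(−hD))/h] / D.

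In an inception cohort the probability is e^(−h). At D = 6, S(0.02) = 0.941 and S(0.20) = 0.568. Back-dated response is then 0.60 × 0.941 / (0.60 × 0.941 + 0.40 × 0.568) = 0.713. The inception cohort gives 0.60 × 0.980 / (0.60 × 0.980 + 0.40 × 0.819) = 0.642. For all four rates at D = 6:

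| Non-responder exit per year | Back-dated | Inception cohort | Excess (points) |
|---|---|---|---|
| 2% | 0.600 | 0.600 | 0 |
| 5% | 0.621 | 0.607 | 1.4 |
| 10% | 0.655 | 0.619 | 3.6 |
| 20% | 0.713 | 0.642 | 7.1 |

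A simulation of 2,000,000 patients per setting agrees with these values to within 0.001. With D = 2 the largest excess is about 1 point (0.652 against 0.642). If half of the patients at a time point are back-dated, the excess is half of that shown, at most about 3.5 points.

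**Step 3: does delayed entry help?** In the same simulation (D = 6), counting year 1 only for patients already enrolled by then gives 0.599, 0.607, 0.620 and 0.643, which matches the inception cohort. Delayed entry therefore removes the excess due to back-dating. It does not remove the ordinary attrition that the inception cohort shares.

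**The case against.** **Pooling is inferred.** The article nowhere states that retrospective interim values will be tabulated together with prospective ones. Table 2 also labels the registry baseline visit as time 0, so time points might run from there. The full protocol and analysis plan are not shown and may separate the groups. This part of the objection stands as a limit on certainty. The article does, however, fix the time origin, the analysis set and the permission for earlier data, and it sets no condition between them. If time points ran from the registry baseline instead, year 1 would mix very different treatment durations, and separation would still be needed.

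**Footnote d of Table 2.** It allows retrospective data, but it is attached only to the rows for medical history and medications, not to the effectiveness tests. That is correct, and the point does not rest on it. The consent wording and Data management are the relevant text.

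**Stronger readings that the document does not support.**

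- A reader might infer that early results do overstate response. No exit data by response are given, and the bias can be zero or negative. Progression is described as slow, so early death is probably a minor contributor.
- A reader might infer that all early-year results come from survivors still on treatment. Patients who start during the registry contribute too, and ever-treated patients who stopped but remain in care can enter.
- A reader might remove 25, 50 or 75% of non-responders and no responders, which turns 0.60 into 67, 75 or 86%. That describes the previously treated group alone, with no responder lost, and ignores pooling.
- A reader might extend the point to the baseline-characteristics regressions. The article names no outcome for them, and a GTR outcome in naïve patients is possible.

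**Selection is acknowledged.** The Discussion mentions self-selection of unknown size and direction and non-participating centres. It does not mention the interval between treatment start and inclusion, which, unlike self-selection, can be handled in the analysis.

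**Conclusion.** The concern holds for the secondary effectiveness summaries by time point. As written, patients treated before inclusion can contribute back-dated early values that are conditional on being alive, in care and consenting at inclusion, and nothing in the article keeps them apart from new starters.

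The direction is not established. Overstatement is the plausible one if non-responders leave care sooner. At a true response of 0.60, with inclusion up to 6 years after treatment start and the exit rates assumed above, the excess in back-dated year-1 response is 0 to about 7 points, and less after pooling. The share of previously treated patients, the delay to inclusion and the exit rates are all assumptions.

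The primary GTR is not affected if naïve means untreated at inclusion. It would be exposed only if naïve means untreated at the start of therapy, and the article leaves that open. This is an inexpensive improvement to descriptive tables and does not undermine the primary outcome.

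**What to change.** 1. In Statistical analyses, present effectiveness by time point separately for patients who start velmanase alfa after inclusion and for those who started before it.
2. For the latter group, count values from inclusion onward, placed at the actual time since treatment start (delayed entry). Show pre-inclusion values in a separate display labelled retrospective.
3. In Effectiveness variables, define velmanase alfa-naïve relative to registry inclusion.

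An indicator for starting before or after inclusion is not needed in the regression models, since it cannot recover patients who never enrolled.

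The cost is a second set of descriptive tables and a few sentences of analysis wording, with no new data. The drawback is fewer patients at the earliest time points in the main display, which matters in an ultra-rare disease. The retrospective display keeps those values visible.
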